1. Prevalence of the target population living with T2D	Participants having biochemical measurement of FBG^b^ (capillary plasma value) ≥126 mg/dl (7 mmol/L) and HbA_1c_^c^ level ≥6.5% [24,40,41]	Measurement of FBG Measurement of HbA_1c_
		Have you ever been told by a doctor or other health worker that you have T2D?
	or Participants reporting use of drugs for T2D, irrespective of their biomarker values	
2. Number of the target population with T2D ever tested for T2D	Classified patients with T2D having had FBG tested in the last 3 years	Have you ever had your blood glucose tested in the last 3 years?
3. Number of those tested ever diagnosed for T2D	Tested patients with T2D reporting ever being told by a doctor or other health worker as having T2D	Have you ever been told by a doctor or other health worker that you have T2D?
4. Number of those diagnosed in care	Diagnosed patients with T2D reporting getting treatment/care for their conditions at least once in the past 12 months	Did you get treatment/care for your T2D condition in the past 12 months?
5. Number of those in care receiving treatment	In-care patients with T2D reporting using drugs for T2D or insulin in the past 2 weeks or in-care patients with T2D reporting following advice to lose weight, stop smoking, do physical exercise, and be on special prescribed diet	Are you currently receiving any of the following treatment/advice for your T2D condition prescribed by a doctor or health care worker? Insulin or drugs (medication) that you have taken in the past 2 weeks Are you currently receiving any of the following treatment/advice for your T2D condition prescribed by a doctor or health care worker? Special prescribed diet and advice to lose weight and advice to stop smoking and advice to start or do more physical exercise
6. Number of those receiving treatment being under control	In-treatment patients with T2D having HbA_1c_ level <8% [24]	Measurement of HbA_1c_ for the known T2D

^a^T2D: type 2 diabetes.

^b^FBG: fasting blood glucose.

^c^HbA_1c_: glycated hemoglobin A_1c_.

**Table 3 table3:** Defined groups of participants for each bar of the cascade of care for HT^a^.

Bars of the cascade of care for HT	Definitions	Questions extracted for analysis
1. Prevalence of the target population living with HT	Participants having systolic blood pressure ≥140 mmHg or diastolic blood pressure ≥90 mmHg [12] or	Measurement of blood pressure (mean of the second and third readings)

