	Participants reporting use of drugs for HT, irrespective of their blood pressure values	Have you ever been told by a doctor or other health worker that you have HT?
2. Number of the target population with HT ever tested for HT	Classified patients with HT having had a blood pressure measured in the last 3 years	Have you ever had your blood pressure measured in the last 3 years?
3. Number of those tested ever diagnosed for HT	Tested patients with HT reporting ever being told by a doctor or other health worker as having HT	Have you ever been told by a doctor or other health worker that you have HT?
4. Number of those diagnosed in care	Diagnosed patients with HT reporting getting treatment/care for their conditions at least once in the past 12 months	Did you get treatment/care for your HT condition in the past 12 months?
5. Number of those in care receiving treatment	In-care patients with HT reporting using drugs for HT in the past 2 weeks or	Are you currently receiving any of the following treatment/advice for your HT condition prescribed by a doctor or other health worker? Drugs (medication) that you have taken in the past 2 weeks
	In-care patients with HT reporting following advice to lose weight, stop smoking, do physical exercise, and reduce salt intake	Are you currently receiving any of the following treatment/advice for your HT condition prescribed by a doctor or other health worker? Advice to reduce salt intake and advice to lose weight and advice to stop smoking and advice to start or do more physical exercise
6. Number of those receiving treatment being under control	In-treatment patients with HT having systolic blood pressure <140 mmHg and diastolic blood pressure <90 mmHg [12]	Measurement of blood pressure (mean of the second and third readings) for the known HT

^a^HT: hypertension.

Because of the multistage stratified random cluster sampling, a 3-stage weighting procedure will be applied to account for (1) the fixed number of villages selected in each OD, (2) the fixed number of households selected in each village, and (3) the number of household members aged 40 and above in each selected household [25,30]. The statistic program Stata 14.2 (StataCorp) [42] will be used to perform the quantitative analyses.

Variables used to generate the cascade of care for T2D and HT are shown in Tables 2 and 3, respectively. The explanatory variables are detailed in Multimedia Appendix 6 [43-47].

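### Table 3 makes it impossible for a hypertensive patient treated by lifestyle advice alone to be counted as under control

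*Protocol article*

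**What the plan says.** The Statistical Analysis Plan section of the protocol article fixes the denominator of each cascade at everyone aged 40 and over classified as having the disease, which is bar 1. For HT, Table 3 defines the bars that matter here as follows.

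- Bar 1, first route: "Participants having systolic blood pressure ≥140 mmHg or diastolic blood pressure ≥90 mmHg".
- Bar 1, second route: "Participants reporting use of drugs for HT, irrespective of their blood pressure values". The question listed beside it is "Have you ever been told by a doctor or other health worker that you have HT", which asks about diagnosis and not about drug use.
- Bar 5, first route: "In-care patients with HT reporting using drugs for HT in the past 2 weeks or".
- Bar 5, second route, which needs no drug: "In-care patients with HT reporting following advice to lose weight, stop smoking, do physical exercise, and reduce salt intake".
- Bar 6: "In-treatment patients with HT having systolic blood pressure <140 mmHg and diastolic blood pressure <90 mmHg".

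Bars 1 and 6 both use the mean of the second and third readings at the survey visit.

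For T2D, Table 2 bar 1 requires fasting blood glucose (FBG) of at least 126 mg/dl together with HbA1c of at least 6.5%, with the alternative "or Participants reporting use of drugs for T2D, irrespective of their biomarker values". T2D control in bar 6 is HbA1c below 8%.

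**The concern.** Defining HT by measured pressure or drug use is coherent when treatment means drugs. Table 3 goes further and lets lifestyle advice alone count as treatment in bar 5, but it does not open bar 1 to match. For someone without drugs, the condition for entering the cascade is the exact opposite of the condition for succeeding in it, on the same readings.

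Three things are at stake. The HT control bar loses the successes of lifestyle management and keeps its failures. The planned regression of the under-control outcome inherits the same selection. Specific aim 4 compares HT cascades between care models, so a difference between districts in how often patients are managed without drugs would appear as a difference in control.

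Separately, the definition column and the question column of bar 1 disagree. Two analysts following Table 3 could build different denominators.

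**Working it through.** **Logic.** The plan gives no figure on this point, so the check starts from the definitions. Assume bars 2 to 4 are passed and that any reported drug use falls within bar 5's two-week window.

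| Survey BP | HT drugs | Bar 5 lifestyle route met | Bar 1 | Bar 5 | Bar 6 |
|---|---|---|---|---|---|
| below 140/90 | no | yes | out | out | out |
| at or above 140/90 | no | yes | in | in | out |
| below 140/90 | yes | either | in | in | in |
| at or above 140/90 | yes | either | in | in | out |

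No row without drugs reaches bar 6. A grid of systolic values from 80 to 220 and diastolic values from 40 to 140 for a drug-free patient gives 0 cells that satisfy both bar 1 and bar 6.

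**Direction.** Let N be all people with HT including x controlled lifestyle-only patients, and C the controlled drug users. The written rule gives C/(N − x). Counting the lost patients gives (C + x)/N. The second minus the first has the sign of x(N − C − x), which is never negative. Dropping these patients cannot raise the control bar, and it lowers it whenever x is above zero and some people with HT are not controlled.

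**Spurious difference between districts (assumed inputs).** Take 100 people with HT in each district, 50 of them treated, and 40% of the treated controlled whether or not they use drugs. The true bar 6 is 20/100 = 20% everywhere. If a share L of the treated is lifestyle-only, 50 × L × 0.40 controlled people are lost from both numerator and denominator.

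| L | Lost | Bar 6 as written |
|---|---|---|
| 5% | 1 | 19/99 = 19.2% |
| 10% | 2 | 18/98 = 18.4% |
| 20% | 4 | 16/96 = 16.7% |
| 40% | 8 | 12/92 = 13.0% |

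Differences between two districts that are truly equal:
- 5% against 10%: 0.8 points
- 10% against 20%: 1.7 points
- 10% against 40%: 5.3 points

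**Understatement within one population (assumed inputs).** Take 550 untreated people with high pressure, 350 drug users of whom 45% are controlled (157.5), and 25 to 150 lifestyle-only patients of whom 30% to 70% are controlled.
- Smallest case (25 patients, 30% controlled, 7.5 lost): 157.5/917.5 = 17.17% as written, 165/925 = 17.84% complete, a gain of 0.7 points.
- Largest case (150 patients, 70% controlled, 105 lost): 157.5/945 = 16.67% as written, 262.5/1050 = 25.00% complete, a gain of 8.3 points.

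**T2D.** Entry needs HbA1c of at least 6.5% and control is below 8%. A drug-free patient with FBG of at least 126 mg/dl and HbA1c from 6.5% to 7.9% is in the denominator and can be under control. Diagnosed drug-free patients with FBG below 126 mg/dl, or with HbA1c below 6.5%, are dropped.

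**The case against.** **The ever-told question may already close the gap.** It is listed in bar 1 of both tables. If the analysts classify on it, diagnosed lifestyle-only patients with normal pressure do enter. But in Table 3 the written definition beside it names drug use, so the question contradicts the definition and does not cure it. The T2D row is visibly broken in the text at hand, so the mismatch should be pressed less firmly there.

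**The group may be small.** Bar 5 joins its four lifestyle items with 'and'. Read literally, someone not advised on weight or smoking is not lifestyle-treated. This stands, and makes a 40% share less plausible.

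**Never has one exception.** Bar 1 puts no time limit on drug use, while bar 5 looks back 2 weeks. A patient who reports drug use but none in that window could enter by the drug route, count as treated by lifestyle, and be controlled. That patient is not managed without drugs, so the point survives for those who report no drug use.

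**The alternative also selects.** Anyone admitted only by reported diagnosis meets the bar 3 diagnosis criterion by definition. This is a real cost and belongs in the fix.

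Three stronger readings are tempting and not supported.
- A reader might infer that T2D has the same fault. It does not, because its entry and control thresholds overlap. The T2D rule can also drop uncontrolled patients, for example FBG 120 mg/dl with HbA1c 9%, so the direction there is open.
- A reader might take control among the treated, 18/48 = 37.5% against 12/42 = 28.6% in the 10% and 40% illustration, and report about 9 points. The plan uses a fixed denominator, where the same case gives 5.3 points.
- A reader might infer that health center and peer educator models are hit hardest because they counsel. The Introduction also says health center staff may start treatment in mild HT and that the peer network supplies low-cost medicines. No document shows that drug-free care differs between districts.

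**Conclusion.** The point holds for HT. By the definitions in Table 3, control among treated patients who report no drug use is zero by construction, and losing the controlled ones understates the HT control bar. This rests on the definition column alone and needs no assumed number.

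The size cannot be determined from the documents. The range of 0.8 to 5.3 points for a spurious difference between districts depends on assumed lifestyle-only shares, on half of those with HT being treated, and on equal 40% control with and without drugs. Distortion of the care-model comparison is conditional on the lifestyle-only share differing between districts, which is possible but not shown. For T2D, what remains is a weaker point: some diagnosed drug-free patients are excluded, without a structural zero.

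**What to change.** Reconcile the bar 1 definition in Table 3 with the question listed beside it by adding a third entry route: an affirmative answer to that question, so that a reported prior diagnosis of HT admits the participant whatever the survey pressure. Add the same route for T2D in Table 2. Report the present definition, by measured value or drug use, as a sensitivity analysis. This concerns classification for analysis only and changes no threshold.

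The cost is two table cells and a recode of answers already collected; the Results section says that analysis was still pending. HbA1c is measured in all known T2D patients, so the added T2D patients can be classified at bar 6.

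State these downsides in the text:
- Some self-reported diagnoses are wrong or resolved.
- People admitted only by the new route meet the bar 3 diagnosis criterion by definition, which raises bar 3.
- The new route also admits diagnosed drug-free people below 140/90 who do not meet bar 5. If x of the newcomers are lifestyle-treated and y are not, bar 6 moves from C/D to (C + x)/(D + x + y), where D is the present denominator. It rises only if x/(x + y) exceeds C/D, so the sensitivity analysis should report x and y by district.

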**Figure 1 figure1:**
[figure not shown]
Flow of the sampling frame.

The sample size of households in all the selected 5 ODs is calculated based on the following formula [30]:

n_h_ = (z^2^)(r)(1–r)(f)(k)/(p)(*γ*)(e^2^)

where n_h_ is the parameter to be calculated and the sample size in terms of the number of households to be selected; z is the statistic that defines the level of confidence desired (1.96 for the 95% level of confidence); r is an estimate of a key indicator to be measured by the survey (the key indicator being T2D prevalence—this r being 0.1 according to 10% of T2D prevalence among adults aged 40 and over—the national STEPS survey 2016 [12]); f is the sample design effect (1.5 used in accordance with the national STEPS survey 2016 [12] and the Cambodian demography and health survey 2014 [19]); k is a multiplier to account for the anticipated rate of nonresponse (1.2 for 20% anticipated rate, as used in the national STEPS survey 2016 [12]); p is the proportion of the total population accounted for by the target population and upon which the parameter r is based (0.24 for 24% [31]); *γ* is the average household size (4.6 for the number of persons per household in the selected provinces—census 2019 [32]); and e is the margin of error to be attained (0.01 for the level of precision at 10% of r).

While HT prevalence is higher, T2D prevalence of 10% [12] is used as the main key indicator of interest to determine the sample size, which is important for the cascade of care. Based on the aforementioned formula, the total sample size would be 5637 households, including 20% of anticipated nonresponse rate. Enlarging the sample size to include enough patients to assure significant differences for the detection of the number of patients with T2D having blood glucose under control would increase the budget 5-fold, which is not feasible. Taking feasibility and budget constraint into consideration, a fixed cluster size of 24 households per village, with 44 villages randomly selected in each OD, will be applied for the sake of controlling the total sample size and interviewer workloads [30]. Thus, a cluster size of 24 households per village over the total villages of 220 would yield the total sample size of 5280 households (also equal 5280 eligible individuals).

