### Target Population and Recruitment Strategy

Adults aged 40 and above are the target population. This age group is appropriate for screening for T2D and HT according to the national standard operating procedure for T2D and HT management in primary care [13]. Other recruitment criteria include (1) being usual members of the household, having stayed in the household the night before the interview or not been absent for more than 6 months; (2) being physically and mentally capable of answering the questions; and (3) providing consent to participate in the study.

The starting point of recruitment is a list of all the eligible households in the selected villages (Multimedia Appendix 3). The list will be constructed by a listing team with support of a local authority, listing households in the selected village having at least one adult aged 40 and above. When a household is selected, 1 household member aged 40 and above will be selected for inclusion in the study. If the selected eligible individual is not present in the household during the first-time visit, 2 repeated callbacks and follow-up will be applied. Only if all these attempts fail, the selected participants would be replaced: the respective households would be replaced with the next household in a row of the eligible household list constructed. The replacement household would be selected following the procedure described earlier. If the eligible individuals can be contacted but express refusal to participate in the study after a few times of failed explanation, the individuals as well as the households would be dropped from the study.

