### Statistical Analysis Plan

For the analysis plan, 6 cascade bars, as explained in Tables 2 and 3, will be used to generate the cascades of care for T2D and HT, respectively. A fixed denominator approach will be followed as it enables readers to see the leakages between stages of the continuum of care [39]. The denominator is the total number of eligible individuals aged 40 and above having T2D (for the T2D cascade of care) and HT (for the HT cascade of care). We will produce the cascade of care for T2D and HT for the selected ODs hosting different existing care models. These cascades of care—in essence, a series of bar charts—will subsequently be translated into cumulative probabilities. The bivariate analysis will be used to identify potential factors associated with the outcome variables—prevalence, testing, diagnosis, in care, in treatment, and under control bars. At the initial stage, the chi-square test will be used to determine the association between explanatory variables and outcome variables. The explanatory variables will include participants’ age, sex, marital status, educational level, household wealth quintile, health care utilization, and care model setting. Variables with statistically significant level (*P*<.2) will be included in a multiple logistic regression model. In addition to the aforementioned variables, BMI, lifestyle, knowledge of T2D and HT, self-management, and social support will be included in the multiple logistic regression model for the outcome variables—in care, in treatment, and under control bars [24,25]. In the multiple logistic regression model, the backward elimination method will be used. The process will start with all the identified explanatory variables. Then, variables with the highest *P* value will be eliminated from the model one by one at a time. The process will be repeated until all the variables in the model are statistically significant with a cut-off point of *P* value <.05. This knowledge will allow us to identify which characteristics stimulate the probability of not reaching the next step in the cascade of care, thereby identifying patient groups not adequately reached.

**Table 2 table2:** Defined groups of participants for each bar of the cascade of care for T2D^a^.

Bars of the cascade of care for T2D	Definitions	Questions extracted for analysis

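### The only stated analytic response to the village-cluster design is a selection weight; no design-based variance is stated for the P values that select variables

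*Protocol article*

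**What the plan says.** **Design.** Sampling and Sample Size makes each operational district (OD) a stratum and villages the primary sampling units. It plans 44 villages per OD, 24 households per village and one person per household. The sample-size formula allows for clustering: "f is the sample design effect (1.5 used in accordance with the national STEPS survey 2016".

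**Analysis.** In the Statistical Analysis Plan, "the chi-square test will be used to determine the association between explanatory variables and outcome variables". Variables with P<.2 enter a multiple logistic model, and backward elimination continues until all remaining P values are below .05. Care model setting is one of the explanatory variables.

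**Link between the two.** One step is tied to the sampling design: "a 3-stage weighting procedure will be applied to account for (1) the fixed number of villages selected in each OD". The other two components are the fixed number of households per village and the number of members aged 40 and above. Stata 14.2 is named, without a survey or cluster-robust procedure.

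**Non-contacts and refusals.** Under Target Population and Recruitment Strategy, when a selected person cannot be found after two callbacks, "the respective households would be replaced with the next household in a row of the eligible household list constructed". Refusing persons and their households are dropped.

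**The concern.** Weights and variance are separate matters. A selection weight removes bias from unequal inclusion probabilities. It does not account for the fact that people in one village resemble each other, so that 24 of them carry less information than 24 independent people. Taking one person per household removes clustering within households but not within villages.

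The plan is therefore uneven. It pays for clustering when it sets the sample size, then gives no matching allowance for the tests. This matters because P values alone decide which factors enter and stay in the models. Standard errors that are too small would let in too many factors. The effect is strongest for covariates shared by a whole village. Care model setting is constant within an OD, and aims 3 and 4 in the Introduction are comparisons between care models.

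The weights raise a second, smaller question. All three components are selection terms, while the recruitment rules allow substitution and dropping of households.

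**Working it through.** **1. The plan's own sample size.** Inputs, all from Sampling and Sample Size: z ("1.96 for the 95% level of confidence"), r ("this r being 0.1 according to 10% of T2D prevalence among adults aged 40 and over"), f = 1.5, k ("k is a multiplier to account for the anticipated rate of nonresponse (1.2 for 20% anticipated rate"), p = 0.24, household size ("4.6 for the number of persons per household in the selected provinces") and e = 0.01.

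n = z² × r(1−r) × f × k ÷ (p × γ × e²) = 3.8416 × 0.09 × 1.5 × 1.2 ÷ (0.24 × 4.6 × 0.0001) = 5637.1.

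This reproduces the stated 5637. The fixed design gives 5 × 44 × 24 = 5280, also as stated.

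**2. Implied intraclass correlation (ICC).** If all of f is clustering, ICC = (f − 1) ÷ (24 − 1) = 0.5 ÷ 23 = 0.0217.

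**3. Error of a test that ignores a design effect D.** For a single contrast, true error = 2 × [1 − Φ(z ÷ √D)], where z is the nominal critical value. At D = 1.5, √D = 1.225, so unadjusted standard errors are 1 − 1/1.225 = 18% too small.
- Nominal .05: 1.960 ÷ 1.225 = 1.600, true error 0.110.
- Nominal .2: 1.282 ÷ 1.225 = 1.046, true error 0.295.

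These hold for a whole-sample outcome (prevalence) and a covariate constant within villages. A test with several degrees of freedom would be inflated more at the same D. I have not sized one, because the article describes four care models in its aims and five OD settings in Table 1.

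**4. Bars restricted to cases.** The achieved sample averages m = 5072 ÷ 220 = 23.05 per village. With prevalence π, the effective cluster size is mπ + (1 − π), and D = 1 + [mπ + (1 − π) − 1] × ICC. The 10% for diabetes is the plan's. The 14.2% for hypertension is the Introduction's figure for ages 18-69. The 30% and 40% for ages 40 and over, and ICCs of 0.05 and 0.10, are assumptions.

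| Bars | Cases per village | D at ICC 0.022 | True error at .05 | D at ICC 0.05; 0.10 | True error at .05 |
|---|---|---|---|---|---|
| Diabetes, 10% | 2.31 | 1.048 | 0.056 | 1.110; 1.221 | 0.063; 0.076 |
| Hypertension, 14.2% | 3.27 | 1.068 | 0.058 | 1.157; 1.313 | 0.068; 0.087 |
| Hypertension, 30% | 6.92 | 1.144 | 0.067 | 1.331; 1.662 | 0.089; 0.128 |
| Hypertension, 40% | 9.22 | 1.192 | 0.073 | 1.441; 1.882 | 0.103; 0.153 |

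The diabetes bars are barely affected at the implied ICC, because each village contributes only two or three cases.

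**5. Nonresponse.** Participation was 5072 of 5280, a shortfall of 208 (3.9%). This is net of substitution, so nonresponse before replacement cannot be recovered. The realised average of 23.05 also means that the number per village was not uniformly 24, as the second weight component supposes.

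**The case against.** A reader might infer that the P values will ignore village clustering. The text does not support that. It names two families of test and no variance estimator, and both families have design-based forms in the software named. The article recognises the design elsewhere, in the strata, the sampling units, the design effect and the Discussion's remarks on clustering. A fuller analysis plan, not shown, may declare all of this. That objection stands against any claim that the analysis will be wrong. It does not remove the mismatch on the page: a section detailed enough to fix screening thresholds, weight components and software release gives one consequence of cluster sampling, and that consequence does not address variance.

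The 11% figure can also be overread. Part of the 1.5 may reflect unequal weighting. Most listed covariates (age, sex, education, wealth) vary within villages and are less affected. Five of the six bars concern cases only. All of this stands, and the figure is used here as an upper end at the plan's own design effect.

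On nonresponse, a reader might infer that substitution tilts the bars toward people found at home, who may be more often in care. The document gives nothing to establish that direction or its size. Two callbacks precede any replacement, and substitutes come from the same village list. If the rule that refusals are not replaced was followed, refusals cannot exceed the 208 shortfall. Calibration to census age-sex margins might also suggest itself, but the frame is the catchments of selected health centers, which census margins may not describe.

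**Conclusion.** The point holds as a gap between design and stated analysis, and it should be closed. If the tests are run as written, with weights but no allowance for villages, true error reaches about 11% at a nominal 5% and about 30% at the P<.2 screen. That is for single contrasts on whole-sample prevalence with village-constant covariates, and assumes that the full 1.5 is clustering. At the implied ICC of 0.022, error is about 6-7% for hypertension bars (assumed prevalence 14-40%) and about 5.6% for diabetes bars. Larger ICCs would raise these figures, but the documents give no ICC.

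The care-model comparison, prevalence and the hypertension cascade are where it matters. The missing nonresponse component is a real but secondary omission that the document does not allow anyone to size.

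**What to change.** State in the Statistical Analysis Plan that OD is the stratum, village the primary sampling unit and the 3-stage weight the sampling weight. Use design-based methods throughout: Rao-Scott chi-square for the P<.2 screen, and survey logistic regression with linearised standard errors for backward elimination. Analyse cases as a subpopulation, so that villages without cases remain in the variance calculation. With 220 villages in 5 strata there are 220 − 5 = 215 design degrees of freedom, which is ample.

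Base the household-stage weight on the realised number of participants per village. If substitutes were flagged during fieldwork, add a sensitivity analysis without them and report the numbers of replaced and refusing households. If they were not flagged, say so as a limitation, since data collection ended in October 2020.

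The cost is small: a few lines of text and survey commands in the Stata release already named, with analysis still reported as pending. Intervals will be somewhat wider and fewer variables may be retained.
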